##### PPIA – Positive psychology–based psychological intervention grounded in the PERMA model via App

2.2.6.1

The PPIA intervention is a structured psychological program grounded in the PERMA model of well-being (20). This model proposes that long-term flourishing depends on developing five pillars: Positive Emotion, Engagement, Relationships, Meaning, and Accomplishment. The intervention is further supported by the broaden-and-build theory of positive emotions (44), flow theory (45), research on character strengths and positive relationships (46, 47), meaning in life (48), the goal-setting theory (49) and growth mindset principles (50).

The program consists of five weekly modules, each lasting approximately 45 minutes and delivered through short daily sessions of 5–10 minutes. Each module includes psychoeducational content, experiential tasks, reflection exercises, and homework assignments designed to facilitate the integration of skills into daily life. Participants are expected to complete one module per week, with daily activities spread across the week (see **Table 1**). If a participant misses a module, the app allows delayed access so that it can be completed before advancing to the next, ensuring adherence to the sequence. The PPIA app is planned as a cross-platform mobile application compatible with iOS and Android devices. Core functions will include secure user authentication, encrypted data transmission through HTTPS/TLS protocols, sequential time-locked delivery of the five weekly modules, automated push notifications, visual progress tracking, and automatic recording of task completion and app engagement metrics. The app will not collect diagnostic risk data or generate automated clinical alerts.

**Table 1 T1:** Contents, materials, and homework of the PERMA-based intervention.

Module	Session contents	Materials and homework
Module 1: Positive Emotion	Introduction to positive emotions; psychoeducation based on the broaden-and-build theory; awareness of positive daily experiences; practicing gratitude and savoring; emotional self-monitoring.	Materials: Short video/audio introduction; mood-tracking tool; gratitude journal template; savoring audio guide. Homework: “Three Good Things” exercise; daily gratitude entries; savoring one positive event; short reflection on emotional changes.
Module 2: Engagement	Understanding strengths vs. talents; identifying personal strengths (VIA framework); introduction to flow experiences; strategies to increase engagement in daily activities.	Materials: VIA strengths short inventory; flow diary template; strength-use instructions; daily progress visualizer. Homework: Complete VIA mini-test; record daily flow experiences; apply 1–2 personal strengths intentionally.
Module 3: Relationships	Psychoeducation on positive relationships; Active-Constructive Responding; empathy-building strategies; expressing appreciation; prosocial micro-actions.	Materials: Appreciation letter template; ACR practice scripts; empathy-walk guide; kindness task list. Homework: Write and optionally deliver an appreciation message; practice active-constructive responding; complete 2–3 micro-acts of kindness.
Module 4: Meaning	Exploring values and purpose; differences between happiness and meaning; identifying meaningful activities; connecting daily actions with personal values.	Materials: Life Compass worksheet; values clarification exercise; purpose-journaling prompts; meaning tracker. Homework: Daily intention-setting; 3-day purpose journal; future-self/legacy letter; one value-aligned action per day.
Module 5: Accomplishment	Goal-setting theory; developing self-efficacy; SMART goals; recognizing and reinforcing progress; planning achievable daily actions.	Materials: SMART goal planner; daily small-wins tracker; best-possible-self visualization; progress chart. Homework: Create weekly SMART goal; record daily small wins; complete Best Possible Self writing task; obstacle-planning reflection.

VIA, Values in Action; ACR, Active-Constructive Responding; SMART, Specific, Measurable, Achievable, Relevant, and Time-bound.

The app offers short-format tasks (5–10 minutes each) to be completed throughout the week. Each module includes a video or audio-based psychoeducational introduction (2–3 minutes), three to five experiential tasks with instructions, logging, and reflection, a personal journal to document insights and responses, interactive visualizations and self-monitoring tools (e.g., mood, progress), and daily motivational messages and reminders. In addition, participants will be assigned specific homework activities each week, such as keeping a gratitude journal, practicing mindfulness, or applying character strengths in daily life. These tasks are designed to consolidate learning, foster habit formation, and increase transfer of skills to real-world contexts.

In the first week, dedicated to Positive Emotion, the objective is to increase awareness, frequency, and intensity of positive affect in daily life. The psychoeducational component highlights the physiological, cognitive, and social benefits of cultivating positive emotions. Activities include *Three Good Things*, a daily gratitude journal organized by life domains, a savoring practice guided by mindfulness audio, and a positive visualization of a future joyful event, with supplemental mood tracking and a brief daily gratitude pause.

The second week, focused on Engagement, aims to help participants identify and apply their personal strengths to increase flow experiences. The module explains the distinction between talents and strengths and the benefits of using strengths regularly. Activities include completing an abbreviated *Values in Action (VIA) Character Strengths Inventory* with feedback, keeping a three-day flow diary, applying strengths in daily tasks, and mapping obstacles to engagement, supported by a strength-use tracker and daily reflections on moments of vitality.

Week three, on Relationships, is designed to enhance relational satisfaction through empathy, appreciation, and active-constructive communication. The psychoeducational content emphasizes the role of supportive interactions in improving health and well-being. Participants write and optionally deliver an appreciation letter, practice active-constructive responding, undertake an empathy walk to adopt others’ perspectives, and perform micro-acts of kindness, complemented by daily ratings of social connection and journaling moments of compassion.

In the fourth week, devoted to Meaning, the goal is to help participants connect everyday actions to their personal values and life purpose. The module distinguishes between happiness and meaning and provides strategies for clarifying values. Activities include completing the *Life Compass* to map personal values, daily purpose journaling, writing a legacy letter to the future self, and tracking value-aligned activities, supported by morning intention-setting prompts and evening reflections on value expression.

The fifth and final week, focusing on Accomplishment, aims to develop goal-setting skills, build self-efficacy, and encourage recognition of personal progress. The psychoeducational content outlines the benefits of celebrating incremental achievements. Activities include creating a *Specific, Measurable, Achievable, Relevant, and Time-bound (SMART)* goal plan with milestone breakdowns, recording daily small wins, engaging in the best possible self-visualization, and reflecting on potential obstacles while developing commitment strategies.

##### PPIA+M – App-based intervention plus multiconference group support

2.2.6.2

Participants assigned to this condition will receive the same five-week mobile intervention as those in the PPIA group, with the addition of a weekly 30-minute telephone-based multiconference session. These sessions will be conducted in small groups (5–6 participants) and facilitated by licensed psychologists or doctoral students trained in group interventions. At the beginning of the first telephone multiconference session, facilitators will explain confidentiality, privacy, and safety rules. Participants will be asked not to disclose information shared by other group members outside the session and may use a preferred first name or pseudonym during calls. They will also be instructed to join the sessions from a private location whenever possible and to use headphones. Each weekly multiconference session will follow a standardized 30-minute structure: a 5-minute check-in, a 10-minute review of completed homework, a 10-minute feedback segment, and a 5-minute wrap-up. Throughout the five sessions, positive or corrective feedback will be delivered in accordance with Miltenberger’s guidelines (51) after reviewing the completed homework. Feedback should be provided immediately after the target behavior and include descriptive praise for correct performance or effort. Corrective feedback should be non-negative, focus on improvement, address one aspect of behavior at a time, and be preceded by praise. Participants will also be encouraged to support one another throughout the change process. Facilitators will be responsible for maintaining time equity, preserving the structured behavioral focus of the session, managing participant interaction around app-based tasks, and ensuring that confidentiality, privacy, and safety rules are followed. If severe distress, suicide risk, trauma-related disclosure, or interpersonal conflict emerges during a call, the facilitator will redirect the group process and activate the Crisis Disclosure Protocol, including private follow-up and referral or emergency procedures when necessary.

##### WLCG – Waitlist Control Group

2.2.6.3

Participants assigned to the Waitlist Control Group (WLCG) will not receive any intervention during the five-week study period but will complete all study assessments at the same time points as the experimental groups. After completing the final follow-up evaluation, participants in the WLCG will be granted access to the full PPIA mobile intervention program.

#### Outcome measures

2.2.7

Participants will be assessed at three key time points: pre-intervention (T1), post-intervention (T2), and six-month follow-up (T3), using the instruments listed in **Table 2**. The evaluated variables will include sociodemographic, academic, and clinical characteristics; presence of mental disorders; emotional well-being; psychological, emotional and social well-being; positive emotion; engagement; relationships; meaning; accomplishment; treatment adherence and dropouts; and satisfaction with the intervention, following the same order presented in **Table 2** and **Figure 1**. All evaluations will be conducted in person by independent psychologists blinded to the study’s objectives, hypotheses, intervention conditions, and group assignments. Evaluator training will be provided by two senior psychologists with extensive experience in psychological assessment and intervention studies, consisting of 20 hours of theoretical and practical seminars, including role-playing scenarios and supervised mock assessments to ensure standardized administration of the instrument. A random sample of 10% of the screening interviews will be audio-recorded and independently rated by a second independent blinded psychologist. Interrater agreement for the final eligibility decision (eligible vs. excluded) will be calculated using Cohen’s kappa, with κ ≥.80 considered the minimum acceptable threshold. Any discrepancies will be resolved by consensus with the senior supervisors.

**Table 2 T2:** Variables, measurement instruments, and administration format.

Variable	Measurement instrument	Administration format
Sociodemographic, academic and clinical characteristics	Sociodemographic, academic, and clinical questionnaire	Hetero-administered
Mental disorders	Structured Clinical Interview for DSM-5, Clinician Version (SCID-5-CV; First et al., 2015)	Hetero-administered
Primary outcomes		
Emotional well-being	Warwick–Edinburgh Mental Well-Being Scale (WEMWBS; Tennant et al., 2007)	Self-administered
Psychological, emotional, and social well-being	Mental Health Continuum–Short Form (MHC-SF; Keyes, 2002)	Self-administered
Secondary outcomes		
Positive emotion	Positive and Negative Affect Schedule (PANAS; Watson et al., 1988)	Self-administered
Engagement	Utrecht Work Engagement Scale–Student Version (UWES-S; Schaufeli & Bakker, 2003)	Self-administered
Relationships	Social Connectedness Scale (SCS; Lee & Robbins, 1995)	Self-administered
Meaning	Meaning in Life Questionnaire (MLQ; Steger et al., 2006)	Self-administered
Accomplishment	Achievement Goal Questionnaire–Revised (AGQ-R; Elliot & Murayama, 2008)	Self-administered
Satisfaction with the intervention	Satisfaction with the intervention: Client Satisfaction Questionnaire–8 (CSQ-8; Larsen et al., 1979; Vázquez et al., 2019, Spanish version)	Self-administered
Treatment adherence and dropouts	Recording of the number of modules completed, between-session tasks performed, attendance at the weekly 30-minute multiconference sessions, and dropouts and time	Hetero-administered

SCID-5-CV, Structured Clinical Interview for DSM-5 Disorders, Clinician Version; WEMWBS, Warwick–Edinburgh Mental Well-Being Scale; MHC-SF, Mental Health Continuum–Short Form; PANAS, Positive and Negative Affect Schedule; UWES-S, Utrecht Work Engagement Scale–Student Version; SCS, Social Connectedness Scale; MLQ, Meaning in Life Questionnaire; AGQ-R, Achievement Goal Questionnaire–Revised; CSQ-8, Client Satisfaction Questionnaire–8.

##### Sociodemographic, academic, and clinical characteristics

2.2.7.1

To collect information on sociodemographic, academic, and clinical variables relevant to participant eligibility, a structured interviewer-administered questionnaire will be used at baseline. It will include information on sex assigned at birth, gender identity, age, marital status, living arrangements, rural/urban setting, employment status, and self-reported socioeconomic level (e.g., monthly household income and access to financial resources). Academic variables will include the current academic program and year of enrollment. Clinical data will include having initiated psychological or psychopharmacological treatment within the two months prior to the study, and currently participating in another mental health–related research study.

##### Presence of mental disorders

2.2.7.2

For the diagnostic interview, the Structured Clinical Interview for DSM-5-Clinician Version (SCID-5-CV (52)) will be conducted to confirm the presence of any mental disorder, in line with the study’s exclusion criteria. The SCID-5 evaluates a wide range of psychiatric conditions according to DSM-5 criteria, including mood, anxiety, psychotic, dissociative, substance-related disorders, and suicidality, among others. It is considered the gold standard diagnostic tool, with high inter-rater reliability (k = 0.76–0.93).

##### Primary outcome measure: psychological well-being

2.2.7.3

The primary outcome of the study will be psychological well-being, operationalized through two co-primary measures: global positive mental well-being assessed with the Warwick–Edinburgh Mental Well-Being Scale (WEMWBS (53)) and emotional, psychological and social well-being assessed with the Mental Health Continuum–Short Form (MHC-SF (54)).

The WEMWBS (53) is a 14-item self-report scale designed to measure positive mental well-being as a central component of optimal psychological functioning. Each item is rated on a 5-point Likert scale, ranging from 1 (“none of the time”) to 5 (“all of the time”), producing a total score from 14 to 70, with higher scores reflecting greater well-being. The WEMWBS has demonstrated excellent internal consistency, with Cronbach’s α typically exceeding .88 across samples, and strong test–retest reliability. Validation studies in Spanish university populations confirm its robust psychometric performance, with α values above .85 and expected associations with related constructs of well-being and mental distress.

The MHC-SF (54) is a widely used instrument for assessing emotional, psychological, and social well-being. It consists of 14 items covering positive affect, personal functioning, and social connectedness, each rated on a 6-point scale, ranging from 0 (“never”) to 5 (“every day”). For the present study, the continuous scoring method will be applied, producing scores ranging from 0 to 70, with higher scores indicating greater positive mental health. The MHC-SF has shown excellent reliability, with internal consistency ranging from α = .80 to .89 in community and student populations. Evidence from Spanish validation studies demonstrates high internal consistency (α = .83–.89), strong construct validity, and sensitivity to changes in well-being among university students.

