###### Positive emotion

2.2.7.4.1

Positive emotion will be assessed with the Positive and Negative Affect Schedule (PANAS (55)), a 20-item self-administered instrument that evaluates the frequency of positive and negative affective experiences. It consists of two 10-item subscales (positive and negative affect), each rated on a 5-point Likert scale ranging from 1 (“very slightly or not at all”) to 5 (“extremely”). The PANAS has demonstrated high internal consistency (α = .86–.90 for the Positive Affect subscale; α = .84–.87 for the Negative Affect subscale) and good convergent and discriminant validity across clinical and non-clinical populations, including university students.

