###### Relationships

2.2.7.4.3

Relationships will be assessed with the Social Connectedness Scale (SCS (57)), an 8-item self-administered instrument that evaluates the degree of interpersonal closeness and belonging. Items are rated on a 6-point Likert scale (1 = “strongly disagree” to 6 = “strongly agree”), with higher scores reflecting stronger connectedness. The SCS has demonstrated excellent internal consistency (α = .91) and robust construct validity across diverse populations, including students.

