##### Moderation and mediation analyses

2.2.9.2

Moderation and mediation analyses will be conducted as exploratory and hypothesis-generating analyses for the PPIA, PPIA+M, and WLCG groups. These analyses are not part of the primary confirmatory testing framework and will not be interpreted as demonstrating causal mechanisms.

Moderation analyses will be conducted using regression models including treatment condition, the candidate moderator, and the treatment-by-moderator interaction term. Continuous variables will be mean-centered to improve interpretation, following the recommendations of Kraemer and Blasey (65). Potential moderators will include baseline sociodemographic, academic, and clinical variables, adherence, and satisfaction with the intervention. Evidence of moderation will be considered present when the treatment-by-moderator interaction term is statistically significant, indicating that the effect of the intervention on well-being outcomes varies according to the level of the moderator.

Mediation analyses will examine whether changes in PERMA dimensions —positive emotion, engagement, relationships, meaning, and accomplishment— are associated with changes in emotional well-being and psychological, emotional, and social well-being. Changes in WEMWBS and MHC-SF scores between baseline and post-intervention will be used as dependent variables, treatment condition as the independent variable, and changes in PERMA dimensions between baseline and post-intervention as potential mediators. Indirect effects will be estimated using bias-corrected bootstrap confidence intervals with 5,000 resamples. Because mediator and outcome changes are assessed over overlapping time intervals, these analyses will be considered exploratory and will not be interpreted as demonstrating causal mechanisms.

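### Two candidate mediators measure constructs that the MHC-SF total also contains, so their mediator-outcome path is partly built in, and the plan's caveat does not say so

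*Protocol article*

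**What the plan says.** Section 2.2.7.3 describes the MHC-SF: "It consists of 14 items covering positive affect, personal functioning, and social connectedness". It adds that "the continuous scoring method will be applied, producing scores ranging from 0 to 70", so all three content areas enter a single number.

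Two of the PERMA dimensions are measured as follows.
- Section 2.2.7.4.1: "Positive emotion will be assessed with the Positive and Negative Affect Schedule (PANAS (55)), a 20-item self-administered instrument". It has a positive and a negative subscale; the positive subscale is taken here as the mediator score.
- Section 2.2.7.4.3: the Social Connectedness Scale (SCS) is "an 8-item self-administered instrument that evaluates the degree of interpersonal closeness and belonging".

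Section 2.2.9.2 then sets up the mediation models: "Changes in WEMWBS and MHC-SF scores between baseline and post-intervention will be used as dependent variables", with "treatment condition as the independent variable, and changes in PERMA dimensions between baseline and post-intervention as potential mediators". Indirect effects are tested with bias-corrected bootstrap intervals from 5,000 resamples.

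The same section places these analyses outside the confirmatory framework and rules out a causal reading. The one specific reason it gives is that mediator and outcome changes are measured over overlapping periods. Neither that section nor the limitations in the Discussion mention overlapping content. The Introduction expects all five dimensions to mediate and wants the results to guide later refinement of the programme. The Discussion says the mediation and moderation analyses will throw light on how the intervention works.

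**The concern.** Two of the three content areas that the protocol names for the MHC-SF are also candidate mediators. If the total contains positive affect, change in any other positive-affect measure will correlate with change in the total, even if positive affect influences nothing else. The same holds for social connectedness and the SCS. Part of the mediator-outcome path is then a property of the questionnaires.

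The module on positive emotion is meant to raise positive affect, and the module on relationships to improve relationships. If either succeeds, the other path is present too, and the model can show an indirect effect with no mechanism behind it. The team could then conclude that these components carry the benefit and build the next version of the programme around them. The time caveat does not guard against this: measuring the mediators earlier would answer the timing problem and leave the shared content in place.

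**Working it through.** **The plan's own figures.** The plan gives no figure for the mediation models. Its sample size is used here only to fix the number per arm, and it reproduces. With f = 0.16, N = 141, 3 groups, 3 times, ρ = .50 and α = .025:
- λ = 0.16² × 141 × 3 / (1 − 0.50) = 21.66, on (3−1)(3−1) = 4 and (141−3)(3−1) = 276 degrees of freedom;
- power 0.9510, against .9509 stated;
- attrition: 47 / 0.8 = 58.75, so 59 per group and 177 in all.

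**Model for the overlap.** Let C be true change in the shared content, R true change in the rest of the MHC-SF, w the weight of the shared content, and M the change on the separate mediator questionnaire with reliability r. C and R have unit variance within arm and, to isolate the overlap, are independent.
- Outcome change: Y = wC + (1 − w)R
- Mediator change: M = √r·C + √(1 − r)·error
- Treatment-mediator path: a = √r × (treatment effect on C)
- Mediator-outcome path given arm: b = w√r
- Indirect effect: a × b = w·r × (treatment effect on C)

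So b is positive whenever w > 0, although C has no influence on R. The product is zero unless treatment moves C.

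**Numbers.** Assumed, not in the documents: w = 0.33, r = 0.5 or 0.8, and an effect of 0.5 SD. The effect of 0.32 SD is the plan's own d/g equivalent. Two arms of 59, 600 simulated trials per setting, 95% bias-corrected bootstrap with 500 resamples. Results are for r = 0.5 / 0.8.

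| Case | Effect on C | Effect on R | C in outcome | a × b by formula | a × b simulated | Interval excludes 0 |
|---|---|---|---|---|---|---|
| 1 | 0 | 0 | yes | 0 / 0 | 0.002 / 0.000 | 7.0% / 7.3% |
| 2 | 0 | 0.5 | yes | 0 / 0 | 0.001 / −0.001 | 6.7% / 6.2% |
| 3 | 0.5 | 0 | yes | 0.083 / 0.132 | 0.082 / 0.135 | 53.5% / 76.7% |
| 4 | 0.32 | 0.32 | yes | 0.053 / 0.084 | 0.052 / 0.086 | 27.5% / 43.2% |
| 5 | 0.5 | 0 | no | 0 / 0 | −0.001 / −0.001 | 4.5% / 6.8% |

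For case 3 the formula gives 0.33 × 0.5 × 0.5 = 0.0825 and 0.33 × 0.8 × 0.5 = 0.132, out of a total effect of 0.33 × 0.5 = 0.165 (simulated 0.17). The share apparently mediated is therefore r itself, 50% or 80%, with no influence of C on the rest of well-being.

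**Sensitivity to the assumptions.** A second simulation used a 5% joint test of both paths, 47 to 59 per arm and r = .6 to .8, with treatment moving only positive affect.

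| Content share | d = 0.32 | d = 0.50 |
|---|---|---|
| one third | 15–32% | 33–66% |
| one fifth | 6–19% | 14–37% |

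With the overlapping items left out of the outcome, the rate was 1–4%. Only positive affect was simulated. The algebra is the same for social connectedness and the SCS, with its own share and reliability.

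**The case against.** A reader might infer that the two mediators are part of the MHC-SF total, so that their indirect effects are true by construction. The documents do not support that. The PANAS and the SCS have their own items and scoring, and neither is a subscore of the MHC-SF: the overlap is of construct. Only the b path is partly built in. In cases 1 and 2 the mean indirect effect is about zero, and even in case 3 it is not always declared.

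Nor do the documents show that the other three mediators are free of overlap. Personal functioning is also named as MHC-SF content and could touch engagement, meaning or accomplishment. For the WEMWBS the protocol gives no item content, so overlap there can be neither asserted nor excluded.

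Three further objections carry weight.
- In case 3 treatment really raises positive affect, and the total really rises because of it. Saying that the gain ran through positive affect is then correct. It is also shallow: it says nothing about whether positive affect changes the rest of well-being, which is what a decision about the programme needs.
- Independence of C and R is artificial, given the internal consistency of .80 to .89 quoted for the MHC-SF. If they correlate at ρ within arm, b = √r[w + (1 − w)ρ]. The overlap term w√r remains, and a score without the shared items leaves only √r·ρ, so the two can be told apart.
- The analyses are already labelled exploratory and non-causal. That protects the confirmatory conclusions and bars a causal claim. It does not remove the built-in part from the association itself, which is what the plan intends to report and use.

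**Conclusion.** The concern holds as a limit on how the exploratory mediation results can be read. By the protocol's own description, the MHC-SF total contains the constructs of two mediators. This inflates their mediator-outcome path, and an indirect effect can follow without any influence on other well-being if treatment moves the shared content. It is not guaranteed.

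Under the assumed one-third share and a 0.5 SD effect, the declared rate is 53.5% to 76.7% with overlap and 4.5% to 6.8% without. With a one-fifth share and d = 0.32 it falls to 6–19%. The direction follows from the algebra. The size depends on content share, reliability of change and treatment effect; the documents give neither the share nor the reliability of change, and their only effect size is the planning value.

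The primary tests, their error control and the sample size are untouched. What is missing is a safeguard against content overlap, since the stated reason for caution concerns timing only.

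**What to change.** In section 2.2.9.2:
1. Keep the full MHC-SF total as the mediation outcome, so that it remains the measure whose treatment effect is being examined.
2. Pre-specify a sensitivity mediation analysis with an MHC-SF score that omits the positive-affect items when PANAS positive affect is the mediator, and omits the social items when the SCS is the mediator. List the omitted items before data are seen.
3. State that an indirect effect that vanishes in this analysis will be interpreted as overlap between measures. Report estimates and intervals from both analyses side by side, because the shorter score also costs some precision.
4. Name content overlap beside the time-interval caveat, and add it to the limitations in the Discussion.
5. Make the same item-content check for engagement, meaning and accomplishment, and for the WEMWBS against all five mediators. Where items overlap, apply the same treatment or report the result as an association between overlapping measures.

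The cost is wording and a few extra model runs, since all items are already collected. The shortened scores will be somewhat less reliable and less comparable with published totals, which is why they belong in a sensitivity analysis and should not replace the full total.
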